#### Statistical analysis plan

All parameters will be assessed for normality using the Kolmogorov-Smirnov test, and homogeneity of variance will be tested using the Levene test. Descriptive statistics will be expressed as the mean ± standard deviation (SD) for normally distributed data and as the median (Q1-Q3) for non-normally distributed data. Mean changes in parameters within the group will be assessed by calculating the difference between pre and postintervention measurements. When the data are normal and the variance is equal, paired *t*-tests will be used to assess the effect of interventions. Differences between groups will be assessed using the variance ANOVA test. Dunnett's test will be used to determine whether there is a significant difference between the experimental and control groups. When the assumptions for parametric tests are not met in the data, non-parametric statistical methods will be used.

Subgroup analyses by sex will be performed to explore whether the effect is modified by sex. The correlations between physiological factors and blood glucose levels will be assessed by Pearson's or Spearman's correlation analysis. Some *post-hoc* exploratory analyses will also be conducted. All analyses will be performed using SPSS version 24.0 (SPSS Inc. Chicago, IL, USA). The criterion for statistical significance will be a two-tailed *p* < 0.05.

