### Randomization and allocation concealment

Stratified randomization will be used. Participants will be stratified by sex. Random number sequences will be generated using SPSS version 24.0 (SPSS Inc. Chicago, IL, USA). A researcher who is independent of the assessment of study outcomes and statistical analysis will perform the random assignments, and grouping code results will be placed in opaque envelopes to ensure group concealment. After inclusion is confirmed, the envelopes will be distributed in the order of inclusion, and the meaning of each group code will not be available to check the grouping status until the beginning of the study. Subjects and staff involved in diet management cannot be blinded, as the participants will consume easily identifiable snacks. Staff assessing clinical outcomes and conducting analysis will remain blinded to the allocation until the statistical analysis is completed.

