### Outcomes

#### Primary outcomes

The change in the MAGE before and after the intervention was chosen as the primary outcome for several reasons. First, MAGE is highly correlated with 24-h urinary 8-isoprostane F2α levels, an indicator of oxidative stress in the body, and increased levels of oxidative stress are in turn significantly and positively correlated with HbA1c in patients with type 2 diabetes (30). Second, MAGE is increased with the progression of atherosclerosis in patients with type 2 diabetes combined with atherosclerosis compared to that in those without atherosclerosis (5). The MAGE data calculated by the CGM assay are more accurate and of some reference value. Other indicators of GV, such as the TIR, area under the curve (AUC), variable coefficient (CV), and mean of daily differences (MODD), are also included in the primary outcomes.

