#### Continuous glucose monitoring

A 2-week CGM system (FreeStyle Libre Flash Glucose Monitoring System, Abbott) will be initiated on the test day at V1. The CGM will be attached to the hypogastrium on the test day morning. Subjects will be asked to measure their blood glucose levels using a glucometer (glucometer 550, Yuwell) four times a day (before breakfast, lunch, dinner, and bedtime) during the CGM measurement period to calibrate the instruments. The CGM will monitor dynamic blood glucose within the next 15 days. To exclude the potential impact of confounders, the data of dynamic blood glucose from D1, D3, D10, and D14 will be excluded in the final analysis, while data from D2 and D9 will be used as baseline values of two intervention periods. We will only use the data from the latter 3 days of each period rigorously and conservatively to maximally control the potential data contamination.

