### Comparisons

First, the three intervention arms will be combined as a group and compared with the control group to evaluate whether the premeal intervention could improve GV. Second, the two arms with high-protein snacks will be combined as a group and compared with the control group; moreover, the high-fat snack arm will be compared with the control group to evaluate whether the two snacks (high-protein and high-fat snacks) could improve GV. If both the high-protein and high-fat snacks show significant improvement effects, we will further directly compare the high-protein snack (combining milk powder and soy powder into one group) with the high-fat snack (almonds) interventions to evaluate which is better. Third, we will also compare the milk powder group with the control group and the soy powder group with the control group, and if both high-protein snack groups show significant improvement, we will further compare the animal protein and plant protein groups directly to verify whether the plant protein group is similar to the animal protein group. Finally, we will compare all the results from different dietary patterns to determine whether premeal snacks have similar effects under habitual diet and standard balanced meals.

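### Within-arm paired t-tests are named as tests of intervention effect, competing with a between-arm analysis that is valid but unadjusted for baseline MAGE and sex

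*Protocol article*

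**What the plan says.** All places are in the protocol article.

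- **Within-arm test (Statistical analysis plan).** "Mean changes in parameters within the group will be assessed by calculating the difference between pre and postintervention measurements". The section then says that, if normality and equal variance hold, paired t-tests "will be used to assess the effect of interventions. Differences between groups will be assessed using the variance ANOVA test".
- **Comparison with control (same section).** "Dunnett's test will be used to determine whether there is a significant difference between the experimental and control groups". The Comparisons section sets out the contrasts, beginning with: "the three intervention arms will be combined as a group and compared with the control group".
- **Outcome scale (Primary outcomes).** "The change in the MAGE before and after the intervention was chosen as the primary outcome for several reasons".
- **Baseline (Continuous glucose monitoring).** "data from D2 and D9 will be used as baseline values of two intervention periods". Each baseline is therefore one day, while the analysed intervention data are the last three days of each period.
- **Sex.** At randomisation: "Participants will be stratified by sex". In the analysis sex appears only here: "Subgroup analyses by sex will be performed to explore whether the effect is modified by sex".

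**The concern.** The trial randomises a concurrent control so that changes over time affecting everyone can be subtracted out. A paired t-test within a snack arm does not do that. It tests whether the arm changed, which combines any snack effect with whatever else differs between the baseline day and the analysed days: a period effect, continuing adaptation to standard meals in the second period, or residual sensor drift. Calling this test the assessment of the intervention gives a no-effect snack a route to a positive claim. The Discussion points the same way when it presents the run-in measurements as making each participant their own control.

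The second issue is precision. With eight per arm, an ANOVA of change scores carries the full noise of a single baseline day, and no baseline covariate or sex term is named to reduce it.

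**Working it through.** **Sample size used.** The dropout step reproduces: 6 / (1 − 0.20) = 7.5, rounded up to 8 per arm, and 4 × 8 = 32. The starting figure of 6 cannot be reproduced, because the margin, SD and power are not given. Nothing below depends on it except that n = 6 is shown as the case after dropout.

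**1. Paired test when the snack does nothing.** Let every arm shift by *s*, in units of the SD of the change. The article gives no value, so *s* = 0.25, 0.5 and 1.0 are assumed. The paired t statistic then follows a noncentral t distribution with n − 1 degrees of freedom and noncentrality *s*√n (for *s* = 0.5 and n = 8, 0.5 × 2.828 = 1.414). At two-sided 0.05 the rejection rates per arm are:

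| Shared shift *s* | n = 8 | n = 6 |
|---|---|---|
| 0 | 5% | 5% |
| 0.25 | 9% | 8% |
| 0.5 | 23% | 17% |
| 1.0 | 68% | 51% |

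In a between-arm comparison of changes the expected difference is *s* − *s* = 0, so the rate stays at 5% for every *s*.

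**2. Change score against ANCOVA.** Two layouts, both with assumed inputs.

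*(a) One-day baseline, outcome the mean of three daily values.* Let one-day MAGE have total variance 1, with between-person part *b* (the one-day reliability) and within-person part *w* = 1 − *b*.
- Change score variance: *w* + *w*/3 = 4*w*/3.
- ANCOVA residual variance: *b* + *w*/3 − *b*².

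| *b* | Change | ANCOVA | Ratio | Reduction |
|---|---|---|---|---|
| 0.3 | 0.933 | 0.443 | 0.475 | 52.5% |
| 0.5 | 0.667 | 0.417 | 0.625 | 37.5% |
| 0.7 | 0.400 | 0.310 | 0.775 | 22.5% |

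*(b) Equal variance before and after, correlation r.* The ratio is (1 − r²) / [2(1 − r)] = (1 + r)/2. For r = 0.3, 0.5 and 0.7 this is 0.65, 0.75 and 0.85, a reduction of 35%, 25% or 15%. A rough penalty for the lost degrees of freedom, 1 + 1/(32 − 4 − 2) = 1.038, moves the ratios to 0.68, 0.78 and 0.88.

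Across both layouts the reduction is roughly 15% to 50%.

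**3. Leaving out sex.** This was simulated with 20,000 trials of four arms of eight, sex balanced within arms, and no arm effect. For an assumed sex difference of 0.5, 1.0 or 1.5 SD in the analysed outcome, the ANOVA without sex rejects in 4.2%, 2.2% or 0.7% of trials. With sex in the model it rejects in about 5%. The omission makes the test conservative.

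**The case against.** The strongest reply is that the efficacy question is already put to a between-arm test. Dunnett's test against control follows directly after the ANOVA sentence, and the Comparisons section addresses whether snacks improve glycemic variability through comparison with control. A reader might infer from the paired-test sentence that the plan ignores its control arm altogether; the article does not support that. What stands against the reply is that no order of precedence is given. The paired test keeps its stated role, and the conditional steps in Comparisons require significant improvement without naming the test that decides it.

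It is also fair that many conceivable time effects are present at baseline or handled by design. The sensor is fitted on D1 and so is already worn on D2, diaries and the alcohol and exercise restrictions run throughout, and D1, D3, D10 and D14 are excluded. This makes a large shared shift less likely. It does not rule one out, and the article gives nothing from which to size it.

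Three further inferences go too far:

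- *That the ANOVA ignores baseline.* The primary outcome is a change, so baseline enters by subtraction, and under randomisation the comparison is unbiased.
- *That omitting sex inflates false positives.* It does the opposite. A stable sex difference in MAGE level cancels from a change score, so only a sex difference in the change matters.
- *That about 55% of such trials would produce a false snack claim.* At *s* = 0.5, 1 − (1 − 0.232)³ = 0.547 is the chance that at least one of three paired tests is significant. It depends on one assumed shift and includes multiplicity: with no shift the figure is already 1 − 0.95³ = 14%.

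Finally, a condensed article may leave covariates to a fuller plan, so the lack of a covariate list would be weak evidence alone. The role given to the paired test is stated outright and does not depend on that.

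**Conclusion.** The concern holds in two parts of unequal weight.

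The paired t-test is wrongly assigned as a test of intervention effect and should be corrected. The direction of the error needs no assumption. Its size does: 9%, 23% or 68% false rejection per arm at n = 8 for assumed shared shifts of 0.25, 0.5 or 1.0 SD of the change. A valid route through ANOVA and Dunnett's test exists, so the fault is a competing route to a claim and not the absence of a controlled comparison.

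The between-arm analysis, read as an ANOVA of change scores, is unbiased but inefficient. The gain from baseline adjustment, roughly 15% to 50% of residual variance, rests on assumed reliabilities or correlations of 0.3 to 0.7. The upper part of that range also assumes that the period outcome is a mean of three daily values. Omitting sex costs power only if sex affects the analysed outcome. This second part is a recommendation for precision, which matters at eight per arm; it does not correct a bias.

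**What to change.** 1. State that within-arm changes are descriptive and are not tests of intervention effect. Apply the same to any non-parametric counterpart.
2. For each period, fit one ANCOVA of period MAGE on arm, baseline MAGE (D2 or D9) and sex.
3. Take the arm comparisons in the Comparisons section, pooled and single, as contrasts of that model, with Dunnett adjustment for single arms against control. State that the conditional steps are decided by these contrasts. The last comparison, between diet patterns, spans both periods and cannot be a contrast of a single-period model, so it needs its own sentence.
4. A log scale is optional.

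The cost is a change of wording and about two residual degrees of freedom (32 − 4 = 28 becomes 26 with all participants analysed). No new data are needed.

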## Methods and analysis

### Study design

This study is a single-center, open-label, multiparallel group, randomized controlled trial. The study consists of two intervention periods: [1] under habitual diet conditions and [2] under balanced standard meal conditions. After a 3-day experiment run-in period, a total of 32 subjects (16 males and 16 females) will be randomized into one of 4 arms in 1:1:1:1 ratio (Figure 1). The 4 arms will include soy powder and milk powder which will be completely dissolved in 250 ml water, almond snacks with 250 ml of water, and a control arm (250 ml of water). Test days will be scheduled before and after the two intervention periods to assess the potential effects of premeal snacks under the habitual diet and standard balanced diet patterns, respectively. During the entire period of this experiment, subjects will be asked to complete a food recording diary (online) including the type, amount, and time of all meals, snacks, and drinks except water (in the form of photos and text). Physical activity and sleep will also be recorded via a mobile app for step count and sleep time records. The study will be performed at Wenzhou Medical University. The protocol followed the Standard Protocol Items: Recommendations for Interventional Trials statement (27).

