#### Blood samples

Fasting venous blood samples will be collected via an anterior elbow vein catheter on the four test days (V1-V4) before and after the two intervention periods. Blood samples will be immediately centrifuged for 15 min (3,000 g at 4°C), frozen at −20°C, and analyzed within 30 days of collection. The analysis will include assessment of fasting glucose, fasting insulin, HbA1c, and C-peptide levels. Plasma glucose will be measured by the glucose oxidase technique. Insulin and C-peptide measurements will be performed by electrochemiluminescence.

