### Statistical methods

#### Sample size determination

The mean amplitude of glycemic excursions (MAGE) was chosen as the primary outcome indicator and it is expected that the MAGE will be reduced by 20% based on a study by Imai (33). Using PASS software (version 11.0), a sample size of 6 participants per group is required using the non-inferiority test for comparison of sample means. Assuming a 20% dropout rate, the sample size required for this study is 8 participants for each group.

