## Discussion

This is the first trial that directly assess the effects of three types of natural snacks on GV. One of the primary aims of this study is to determine which type of snacks is better for GV improvement. Short-term and long-term studies showed that high-protein and high-fat snack interventions could improve glucose metabolism, β cell function, lipid profile, satiety, and body weight, etc. (34–38), while previous experiments also reported that high-protein snacks were better at reducing hunger, bringing satiety, and reducing energy intake for the next meal (39). We hypothesize that all three types of snacks could improve GV and perhaps high-protein snacks have a better effect. In addition, most previous studies focused on separate animal-based protein and suggested that premeal animal protein has a superior effect on glycemic control, probably because of the high branched-chain amino acid content of whey protein, which allows for faster digestion and absorption of milk, causing a significant postprandial amino acid response and rapid first-phase insulin release (40, 41). However, none of these studies assessed the effect of plant-based and animal-based high-protein natural snacks on GV. In this trial, we will directly compare the effects of these two types of high-protein snacks and expect to observe a non-inferiority effect of soy powder compared to milk powder. We also hypothesize a non-inferiority effect of plant-based high-protein snacks (whole soy powder) compared with animal-based high-protein snacks (milk powder) on GV improvement. If this hypothesis is proven, the effective use of soy powder could also provide more options for the lactose-intolerant population.

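### Simple Pearson or Spearman correlation has no arm term: if post-intervention or change values are correlated across the four arms, a snack effect on both variables can appear as a physiological link

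*Protocol article*

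**What the plan says.** One sentence in the Statistical analysis plan covers this analysis: "The correlations between physiological factors and blood glucose levels will be assessed by Pearson's or Spearman's correlation analysis". It names no arm term, other covariate, visit or period. It does not say whether baseline, post-intervention or change values are meant, and it does not list the factors. It stands between the sex subgroup analysis and a mention of post-hoc exploratory work. One criterion is set for the whole section: "The criterion for statistical significance will be a two-tailed *p* < 0.05".

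The design is a four-arm randomised comparison: "a total of 32 subjects (16 males and 16 females) will be randomized into one of 4 arms in 1:1:1:1 ratio".

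The authors expect arm to matter on both sides of such a correlation. On glycemic variability, the Discussion says: "We hypothesize that all three types of snacks could improve GV and perhaps high-protein snacks have a better effect". On the physiological side, the secondary objective at the end of the Introduction is to look for favourable effects on insulin, the HOMA indices, C-peptide, body size and appetite. Fasting glucose, insulin and C-peptide are measured in blood taken "on the four test days (V1-V4) before and after the two intervention periods".

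**The concern.** When treatment moves two variables, arm is a common cause of both. A plain correlation across arms then mixes two things: any relation between the variables among people on the same treatment, and the fact that snack arms and the water arm differ on both. Neither Pearson's nor Spearman's coefficient separates these. The better the snacks work, the more of the pooled coefficient simply restates the treatment effect.

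What is at stake is interpretation. A significant coefficient could be read as a link between, say, insulin and glucose, and so as a hint of mechanism, when it only shows that the snack changed both.

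**Working it through.** **Inputs from the protocol article.** Four arms with equal allocation, 32 participants (Study design). Six evaluable per arm, raised to 8 for 20% dropout (Sample size determination). Two-sided 0.05 (Statistical analysis plan).

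**The plan's own figure.** No figure is given for the correlation analysis. The group size reproduces from its base: 6 / (1 − 0.20) = 7.5, rounded up to 8, and 4 × 8 = 32. Without the expected losses there are 4 × 6 = 24 evaluable participants. The base of 6 cannot be checked, because margin, SD and power are not stated, but nothing here depends on it.

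**Assumptions not in the protocol.** All three snacks shift the physiological variable by dx and the glucose variable by dy, in within-arm SD units, relative to water. There is no correlation inside any arm. Shifts from 0 to 2 SD were tried.

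**Closed form.** A share of 3/4 of participants is in a snack arm, so the snack indicator has variance 0.75 × 0.25 = 0.1875. The correlation across arms is then

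rho = 0.1875·dx·dy / √[(1 + 0.1875·dx²)(1 + 0.1875·dy²)].

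- 0.5/0.5 SD: 0.0469 / 1.0469 = 0.045
- 1/1 SD: 0.1875 / 1.1875 = 0.158
- 1.5/1.5 SD: 0.4219 / 1.4219 = 0.297

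If either shift is zero, rho is zero. Shifts in opposite directions change only the sign.

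**Simulation.** 20,000 trials per row. The table gives the percentage with p < 0.05. The adjusted columns use Pearson correlation partial on three arm indicators.

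| Shift dx/dy (SD) | rho | Pearson, n = 32 | Spearman, n = 32 | Adjusted, n = 32 | Pearson, n = 24 | Adjusted, n = 24 |
|---|---|---|---|---|---|---|
| 0 / 0 | 0 | 5.2 | 5.2 | 5.1 | 5.1 | 5.2 |
| 0 / 1 | 0 | 5.0 | 4.8 | 4.9 | 5.0 | 5.0 |
| 0.5 / 0.5 | 0.045 | 5.6 | 5.3 | 4.8 | 5.4 | 4.7 |
| 1 / 0.5 | 0.084 | 7.7 | 7.5 | 5.3 | 6.7 | 4.7 |
| 1 / 1 | 0.158 | 14.1 | 13.3 | 5.3 | 11.4 | 4.8 |
| 1.5 / 1.5 | 0.297 | 40.0 | 35.6 | 4.9 | 30.2 | 5.3 |
| 2 / 2 | 0.429 | 75.7 | 65.9 | 4.7 | 62.2 | 4.8 |

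Using ranks does not remove the effect; adjusting for arm does, at both sample sizes.

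**Why an across-arm analysis is the likely reading.** A correlation inside one arm reaches p < 0.05 only if |r| exceeds t/√(df + t²). For 8 people (df = 6, t = 2.447) that is 0.71; for 6 people (df = 4, t = 2.776) it is 0.81. Separate analyses in arms of this size could detect only very strong relations.

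**The case against.** The strongest reply is that the sentence does not specify the analysis being criticised. It never says the arms are combined, nor that on-treatment values are used. With baseline values, or correlations inside each arm, the problem does not arise. A condensed article may also leave such detail to a fuller plan. This stands as far as it goes: the point is conditional, and the missing detail alone would not be a finding. What remains is that the article does fix the method, and both named methods are bivariate.

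The second reply concerns size. The protocol gives no SD and no expected shift for any physiological measure. The blood samples are fasting, each period lasts four days and each snack supplies 80 to 90 kcal, so shifts of 1 SD or more in both variables may not occur. This also stands. At 0.5 SD in both the inflation is negligible.

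Third, if a snack moves both variables, the correlation across the mixed population is truly non-zero, and the test is right to detect it. That is correct. The rejection rates above are errors only when the coefficient is read as a relation among people on the same treatment. That is, however, the usual reading of a link between a physiological factor and glucose.

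A reader might also infer, from the four blood-sampling days, that the visits will be stacked as 32 × 4 = 128 independent pairs. The documents do not support this. The Blood samples section says only when blood is drawn, while Secondary outcomes and the Statistical analysis plan point to pre-to-post changes, with each period assessed separately.

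**Conclusion.** The point holds in conditional form and is minor. If post-intervention or change values are correlated across arms, the named methods can present a snack effect on two variables as a link between them. Under the assumed shifts and no within-arm relation, the Pearson rejection rate with 32 participants is about 6% at 0.5 SD, 14% at 1 SD and 40% at 1.5 SD in both variables, against about 5% after adjustment for arm. With 24 evaluable participants the last two fall to about 11% and 30%.

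A reader might go further and conclude that the plan as written will create false correlations. The text does not support that: it does not state that arms are combined, the shift sizes are unknown, and nothing is inflated if only one variable moves. The analysis is also absent from the primary outcomes, the secondary outcomes and the Comparisons section, so no sample size or main conclusion is affected.

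**What to change.** Amend the sentence to say which values are correlated. For post-intervention or change values, replace the simple coefficient with a partial correlation (on ranks where the data call for it) or a linear regression that includes arm and the stratification factor sex. Use one value per participant per period, and label the results exploratory.

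The cost is one sentence and about four degrees of freedom: a simple correlation on 32 participants has 32 − 2 = 30, three arm indicators and one for sex take 4, and 26 remain. The simulations adjusted for arm only, by Pearson partial correlation; the rank version and the added sex term were not simulated. Design, sample size and data collection are unchanged.
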